### Data management

Participants will be coded with a study number after informed consent, and all data referring to patients will be documented by this number, not by name. A case report form (CRF) will be used for participants to collect information including baseline information, radiographic outcomes, and follow-up. Data will be collected at baseline admission and 2 days post-operation, as well as 3, 6 and 12 months post-surgery. Data on adverse events and further medical treatments will also be collected. The recording of data is assigned to a data manager who is accountable for it, and other researchers will be restricted from accessing study data.

### Sample size calculation

The primary outcome of this trial is the CSA and a power analysis was performed using PASS 15 (NCSS LLC, USA) to calculate the sample size. According to the results of Kaiser’s study [26] and our preliminary study, the reduction of CSA was 2.6° ± 1.8° (mean ± standard deviation, SD) in group A, 4.4° ± 1.5° in group B, and 4.8° ± 1.6° in group C respectively. Based on a power of 90%, and an alpha error of 0.05, a sample size of 48 patients was determined. After taking into consideration a dropout rate of 20%, a sample of 60 participants (20 participants per group) will be recruited.

### Statistical analysis

The analysis of covariance will be conducted to compare the alteration of the CSA and shoulder function scores between randomized groups. The accuracy rates of different acromioplasties will be calculated, and χ^2^ test will be performed to evaluate the statistical differences between groups. The Spearman correlation coefficients will be used to assess the relationship between CSA and shoulder function scores. The intraclass correlation coefficient will be calculated to assess the consistency between researchers and between measurements of a single researcher. Statistical significance will be set at *P* < 0.05. All analyses will be carried out using SPSS 19 (IBM Corp, USA) by two researchers blinded to the recruitment and collection.

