#### Post-operative CSA on X-ray

The post-operative CSA of participants will be measured on standard anteroposterior radiography of the shoulder (Fig. 3b). The efficacy is reflected in the reduction of CSA after acromioplasty. The accuracy is defined as the percentage of patients whose post-operative CSA decreased from a large angle (≥33°) to a normal range (30–33°) via acromioplasty.

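### CSA reduction and accuracy both stand as primary, each tested at P < 0.05 with no order, so the chance of a false primary finding is about 9–11% instead of 5%

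*Protocol article*

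**What the plan says.** Under Primary outcome, the subsection on post-operative CSA defines two measures:

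- Efficacy: "The efficacy is reflected in the reduction of CSA after acromioplasty".
- Accuracy: "The accuracy is defined as the percentage of patients whose post-operative CSA decreased from a large angle" (33° or more) into the 30–33° range.

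The Statistical analysis section gives each its own test. For reduction, "The analysis of covariance will be conducted to compare the alteration of the CSA and shoulder function scores between randomized groups". For accuracy, "The accuracy rates of different acromioplasties will be calculated", and a χ² "test will be performed to evaluate the statistical differences between groups". One threshold covers everything: "Statistical significance will be set at" P < 0.05.

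The Sample size calculation says "The primary outcome of this trial is the CSA", a label that fits either measure, and then uses only the reductions expected in the three groups: "Based on a power of 90%, and an alpha error of 0.05, a sample size of 48 patients was determined".

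**The concern.** Two measures stand under the primary heading, each has its own test, and each test uses the full 5%. The article does not rank them, split alpha or say that both must succeed. A significant result on either could therefore be reported as the trial's primary finding, and the 5% in the sample size calculation is not the error rate of that decision.

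Accuracy is not a minor addition. The Background and Discussion present landing in 30–33° as the gap that the new technique fills, and the stated aims pair accuracy with effectiveness. On the sample size figures, groups B and C differ in reduction by only 4.8 − 4.4 = 0.4°. With the stated SDs, power for that pair at 0.05 is about 11% at 16 per group and 13% at 20. Evidence that the precise technique improves on the lateral one would thus more probably come from accuracy, for which the trial is not sized.

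**Working it through.** **1. Inputs from the article.** Expected reductions (mean, SD): A 2.6°, 1.8°; B 4.4°, 1.5°; C 4.8°, 1.6°. Allocation 1:1:1, alpha 0.05, power 90%, N = 48, dropout 20%, 60 recruited.

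**2. Reproducing N = 48.** Take a three-group omnibus F test with a common SD of 1.8, the largest of the three; this choice is inferred, because the article does not state it.

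- Grand mean: 11.8/3 = 3.933.
- Squared deviations: 1.778 + 0.218 + 0.751 = 2.747.
- Noncentrality at 16 per group: 16 × 2.747/1.8² = 13.57, giving power 0.9005 and N = 3 × 16 = 48.
- Recruitment: 48/0.8 = 60.

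The figure is reproduced by one test, on reduction, at the full 0.05. The pooled SD, √((1.8² + 1.5² + 1.6²)/3) = 1.638, would give 14 per group (42). Accuracy plays no part, and no expected accuracy rates are given, so its power cannot be computed.

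**3. Two tests at 0.05.** If independent, the chance of at least one false positive is 1 − 0.95² = 9.75%.

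**4. Allowing for shared data.** Both measures use the same post-operative angle, so the pair was simulated with no group difference, 10,000 trials per setting. Assumptions where the article gives no figure: pre-operative CSA normal (36.5°, SD 2.5°) truncated at 33° and used as the ANCOVA covariate; reduction SD 1.63°; the same mean reduction in all groups.

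| Per group | Mean reduction | ANCOVA alone | χ² alone | At least one | Both |
|---|---|---|---|---|---|
| 16 | 2.6° | 4.50% | 5.10% | 9.11% | 0.49% |
| 16 | 4.0° | 4.82% | 5.34% | 9.87% | 0.29% |
| 16 | 4.8° | 4.90% | 5.38% | 10.08% | 0.20% |
| 20 | 2.6° | 5.39% | 5.35% | 10.06% | 0.68% |
| 20 | 4.0° | 4.80% | 5.14% | 9.63% | 0.31% |
| 20 | 4.8° | 5.42% | 5.14% | 10.35% | 0.21% |

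Simulation error is about √(0.1 × 0.9/10,000) = 0.3 percentage points. Each test alone holds about 5%. Sharing the same angle gives almost no protection. A separate run of the same pair of tests put the error at about 9–11%.

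**5. If pairwise tests were run without a gate.** Three reduction pairs would give about 11–13%. Six pairs over both measures would give about 21–23% (1 − 0.95⁶ = 26.5% if independent). These describe an analysis that the article does not specify.

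**6. Checking the remedy.** Suppose a significant reduction omnibus opened both the reduction pairs and accuracy at 0.05 in parallel. Take A at 2.6°, B and C both at 4.6°, SD 1.638°, and equal accuracy of 30% or 50%, independent of reduction (all assumed). The gate then usually opens, and two true null hypotheses remain: B equals C, and equal accuracy. Theory gives close to 1 − 0.95² = 9.75%, and simulation at 16 or 20 per group gave about 9–10%. The steps after the gate therefore need a single order.

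**The case against.** **The article does rank the measures.** It names one primary outcome in the sample size section, sizes on reduction, and lists the CSA change first in the analysis section. This makes reduction the natural candidate. It does not settle the matter, because accuracy is defined under the primary heading and has its own significance test.

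**This is a journal article, and multiplicity rules may sit in an analysis plan.** That stands for the detail of post-hoc comparisons, whose absence is not held against the article. The point rests on what is stated: two measures under the primary heading, two tests and one flat threshold.

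**Stronger readings.** A reader might infer that any of six pairwise results could become the primary finding, with an error above 20%. The text does not support this. Both tests are naturally read as three-group omnibus tests, no pairwise comparison is planned, and with exactly three groups pairwise tests made only after a significant omnibus add no inflation within a measure. A reader might also count pre-operative CSA as a third primary test, because it has a subsection under that heading. It is a baseline measurement and eligibility criterion, and no between-group test of it is planned.

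**Milder readings.** If both measures had to succeed, the error would be only 0.2–0.7%, but no such rule is stated. Also, N = 48 would follow from the pooled SD of 1.638 at alpha 0.025 (power 0.907), which might suggest a silent split. The article states 0.05 in both places.

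**Conclusion.** The point holds for the two measures. Followed as written, the two omnibus tests give at least one false primary finding in about 9–11% of trials when the techniques do not differ, about twice the stated 5%. The 9.75% needs only independence; the simulated range rests on the assumed pre-operative CSA distribution, a reduction SD of about 1.64°, common mean reductions of 2.6–4.8° and 16–20 patients per group. The result varied little across the mean reductions and group sizes tried. The defect does not invalidate the trial, but it should be corrected before analysis.

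**What to change.** In the Primary outcome, Sample size calculation and Statistical analysis sections:

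- **Primary.** Name CSA reduction, the measure on which the trial is sized, as the single primary outcome, tested by the three-group ANCOVA at 0.05. Make pairwise reduction comparisons only if that test is significant; with three groups this holds the familywise error for reduction at 5%.
- **Accuracy.** Make it the key secondary outcome, reported with 95% confidence intervals. If a formal claim is wanted under the same 5%, write down one order after the omnibus gate: for example, the reduction pairs in a fixed order, then the accuracy omnibus, then accuracy pairs only if that is significant. Do not open the reduction pairs and accuracy in parallel.
- **Labelling.** List pre-operative CSA as the baseline value and ANCOVA covariate. This has no effect on the error rate.

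The sample size stays at 48 and 60. The cost is that accuracy cannot be formally claimed once an earlier step fails. The place of the B–C reduction pair matters here: with power of about 11–13%, putting it ahead of accuracy would usually block the accuracy test, so its position should be chosen deliberately.

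The alternative of 0.025 for each measure (familywise error 1 − 0.975² = 4.9%) costs more at the SD of 1.8 that reproduces N = 48: power at 16 per group falls from 90.1% to 83.7%. Restoring 90% needs 19 per group (57), or 57/0.8 = 71.25, so 72 recruited in equal groups. At the pooled SD of 1.638, 48 would still give 90.7%.

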## Discussion

The critical shoulder angle (CSA), which combines the measurements of the lateral extension of the acromion and the inclination of the glenoid joint plane, was originally introduced by Moor et al. [12]. They documented that degenerative rotator cuff tears (RCTs) had significantly larger CSAs (≥35°) than asymptomatic shoulders without this pathology, and that a CSA smaller than 30° is associated with glenohumeral osteoarthrtitis (OA). Gerber et al. confirmed these conclusions through a biomechanical analysis which demonstrated that a high CSA could induce supraspinatus (SSP) overload and that a low CSA increased the pressure of the humeral head on the glenoid [29–31]. To date, altering the CSA by arthroscopic acromioplasty is a common strategy. In 2017, Gerber et al. first demonstrated that the mean CSA was significantly corrected from 37.5° pre-operatively to 33.9° post-operatively through lateral acromioplasty in vivo [20]. Billaud et al. first reported in a clinical study that the average CSA decreased from 35.9° to 33° after anterolateral acromioplasty (anterior third of the acromion to be resected) [24]. Although arthroscopic acromioplasty is an effective procedure to decrease CSAs, questions remain regarding the necessity of acromioplasty performed alongside rotator cuff repair (RCR) has never ceased [32]. Several studies have found no difference in patient-reported outcome scores for patients who had arthroscopic RCR with or without acromioplasty [33–35]; besides, the reduction of the CSA does not improve functional results postoperatively [36, 37]. Conversely, some authors have demonstrated that large CSAs increase the risk of re-tearing after RCR [38–41]. Gerber et al. showed that abnormally large CSAs are associated either with higher re-tear rates or with inferior strength of abduction after reconstruction [20]. As most of these authors suggested, we recommend that if the CSA is greater than 33°, acromioplasty should be performed during arthroscopic RCR to reduce large CSAs to normal range (30–33°) [21].

Although lateral acromioplasty has been documented to be the most effective way to decrease CSAs in vitro [22, 26], the post-operative angle is uncontrollable due to the insufficient or over-resection of the acromion. In other words, this is not always correct the large CSAs into the desired range of 30–33°. Additionally, lateral acromioplasty up to 10 mm has been considered a safe technique [20, 22, 42], yet some authors reported that over-resection of the acromion has potential complications, such as detachment of the deltoid origin and acromial fractures [43–45]. In 2017, Karns et al. introduced the concept of the critical acromion point (CAP), which is the most inferolateral part of the acromion and the key point used to determine the degree of the CSA on true anteroposterior radiograph. They also proposed a virtual acromioplasty on three-dimensional (3D) scapulae models with resection of the acromion parallel to the glenoid face of 2.5/5 mm medial to the CAP [46]. This technique seemed to have the equivalent effect in altering the CSA while preserving more bone volume when compared with lateral acromioplasty. However, only 80% of specimens with a native CSA of 38° or greater could be decreased to the acceptable range by this virtual acromioplasty; in addition, this technique has not been clinically realized so far.

To addresses the aforementioned deficiencies, we developed a precise acromioplasty technique, which is an individualized therapeutic strategy oriented by pre-operative virtual acromioplasty on 3D-CT model and software analysis, for the purpose of reducing the CSA with greater efficacy and accuracy. Theoretically, we can clinically decrease large CSAs to any desired specific angle by this technique without cutting acromion not contributing to the CSA. Additionally, we will conduct a prospective randomized clinical trial to examine patients with RCTs and a CSA of 33° or greater who undergo acromioplasty during arthroscopic RCR to evaluate the impact of different acromioplasties. This study will provide a new precision and individualized treatment to reduce CSA.

## Data Availability

The results of this trial will be made available upon request by the corresponding author.

## Abbreviations

ASES: American Shoulder and Elbow Surgeon Shoulder Assessment Form
BMI: Body mass index
CAP: Critical acromion point
CRF: Case report form
CSA: Critical shoulder angle
CSS: Constant Shoulder Score
DICOM: Digital Imaging and Communications in Medicine
MRI: Magnetic resonance imaging
OA: Osteoarthritis
RCR: Rotator cuff repair
RCTs: Rotator cuff tears
SLAP: Superior labrum from anterior to posterior lesion
SSP: Supraspinatus
3D-CT: Three-dimensional computed tomography
UCLA: University of California at Los Angeles score
VAS: Visual analog scale score
